### Power and expected benefit

The needed sample size estimation was done by the following assumptions:

The prevalence of AAA and PAD is 4% and 8% respectively. The five year mortality risk in case of AAA or PAD is 28% oppose to 15% in the control group. Statin-lowering or antiplatelet medication can be initiated in one-third of the diagnosed men with PAD or AAA and causes a relative all cause mortality risk reduction of 20%. AAA-related death within five years is 1% but screening reduces this with 50%. The expected screening attendance is 75%

If so, the needed sample size is 2 × 23,604 (5% significance level and 90% power) and approx. 250 lives will be saved. If the ten year mortality in the control group is 36% [3], and if the relative risk is maintained, the needed sample size is 2 × 7,500, corresponding to 2.5% absolute mortality risk reduction and 590 lives saved corresponding to 40 men needed to screen to prevent one death.

These calculations must be considered to be conservative and the potential benefit by diagnosing new hypertensives is not included.

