## Background

It has been demonstrated that abdominal aortic aneurysm (AAA) screening of men aged 65-74 years reduces AAA mortality. Research at Viborg Hospital published in the British Medical Journal in March 2005 [1] shows that only 352 Danish men above the age of 65 require AAA screening to avoid one AAA rupture-related death in the subsequent 5-year period. Furthermore, it seems that the long-term economic efficiency of screening is at a level, which is generally considered cost effective, at least from a health care sector perspective [2-4]. Despite the clinical and economic evidence for the attractiveness of population screening, few national health care services have implemented permanent programs.

The majority of AAAs diagnosed by screening does not comprise a rupture risk due to being detected early, but nearly half expand to sizes requiring repair. However growth may be limited through smoking cessation [5,6], low-dose aspirin [7-9], statin treatment [10] and ACE inhibitor therapy [11] which will ultimately also reduce the increased cardiovascular risk of the affected patients [12].

International studies indicate that approximately 5-10% of men above the age of 60 show signs of peripheral arterial disease (PAD; ankle brachial systolic blood pressure index (ABI) <0.9) - a proportion which increases with age, and mainly non-symptomatic. Approximately 25-30% of these men will die from cardiovascular disease within a 5-year period, and an even higher proportion will need hospitalization due to cardiovascular disease. Cholesterol-lowering, smoking cessation, low-dose acetylsalicylic acid (aspirins), exercise, a healthy diet and blood-pressure control reduce the increased risks for cardiovascular disease by at least 20-25% [13-16]. So far, screening studies have neglected the interaction between PAD-screening and such general prophylactic efforts, and thus the benefit and cost effectiveness of screening may be underestimated.

In sum, well-documented health benefits may be achieved through prophylactic screening for cardiovascular disease. Advantages include fewer premature deaths and a reduction in the number of amputations and hospital admissions. Furthermore, hospital costs may be reduced by the decrease in admissions and in-hospital post-operative care.

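### The stated sample sizes, power and lives saved do not follow from the listed assumptions, which give about 38–54% power at five years instead of 90%

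*Protocol article*

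**What the plan says.** The Protocol article, section Power and expected benefit, gives these inputs:

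- Prevalence: "The prevalence of AAA and PAD is 4% and 8% respectively".
- Five-year mortality: "The five year mortality risk in case of AAA or PAD is 28% oppose to 15% in the control group".
- Medication: "can be initiated in one-third of the diagnosed men with PAD or AAA and causes a relative all cause mortality risk reduction of 20" per cent.
- AAA-related death: 1% over five years, halved by screening.
- Attendance: 75%.

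It then presents the result as a consequence of these inputs: "the needed sample size is 2 × 23,604 (5% significance level and 90% power) and approx. 250 lives will be saved". With 36% control mortality at ten years and the same relative risk, it states that "the needed sample size is 2 × 7,500, corresponding to 2.5% absolute mortality risk reduction and 590 lives saved", which it also expresses as 40 men screened per death prevented. It closes with "These calculations must be considered to be conservative" and adds that any benefit from newly found hypertension is left out. The section Analysis of efficacy specifies intention to treat, and the primary outcome is all-cause mortality.

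**The concern.** Under intention to treat, the effect is averaged over every invited man. Only about 12% have either condition, a quarter do not attend, and medication is newly started in one third of those diagnosed. After that dilution, a 7% relative reduction in all-cause mortality looked too large for the inputs given.

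Major follow-up is planned at 3, 5 and 10 years, and the conclusions address policy-makers. A null five-year mortality result would be read against a published claim of 90% power. The ten-year claims of 590 lives and one death averted per 40 men would likewise set expectations that the protocol's own inputs do not support.

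**Working it through.** **1. The effect behind the stated results.** The lives-saved figures show it directly, whatever test is used: 250 / 23,604 = 1.06 points at five years and 590 / 23,604 = 2.50 points at ten years. As a check on the sizes, the two-proportion formula with two-sided 5% and 90% power is

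n per arm = (1.960 + 1.2816)² × [p1(1−p1) + p2(1−p2)] / (p1−p2)².

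- Five years, risk ratio 0.93: 15% v 13.95%. n = 10.507 × (0.1275 + 0.1200) / 0.0105² ≈ 23,592 (23,595 with pooled variance under the null). Lives saved: 23,604 × 0.0105 = 248.
- Ten years, risk ratio 0.93: 36% v 33.48%. n = 10.507 × (0.2304 + 0.2227) / 0.0252² ≈ 7,497 (7,500 pooled). Lives saved: 23,604 × 0.0252 = 595. Men invited per death averted: 1 / 0.0252 = 40.

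One risk ratio, 0.93, therefore reproduces every stated result closely. The section neither states nor derives it.

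**2. The effect that the listed inputs give.**

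- Medication: (0.04 + 0.08) × 0.75 × 1/3 × 0.28 × 0.20 = 0.00168, or 0.168 points.
- AAA: 0.01 × 0.50 = 0.50 points if the halving already refers to all invited men; × 0.75 = 0.375 points if attendance applies.
- Total: 0.543 or 0.668 points. Risk ratio: 1 − 0.543/15 = 0.964, or 1 − 0.668/15 = 0.955.

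**3. What follows from that effect** (pooled formula, two-sided 5%):

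| Quantity | Stated | Attendance on both parts | Attendance on medication only |
|---|---|---|---|
| Five-year difference, points | 1.05 (implied) | 0.543 | 0.668 |
| Five-year power, 23,604 per arm | 90% | 38.4% | 53.6% |
| Five-year lives saved | 250 | 128 | 158 |
| n per arm for 90% power, five years | 23,604 | 89,512 | 58,938 |
| Ten-year difference, points | 2.5 | 1.30 | 1.60 |
| Ten-year lives saved | 590 | 308 | 378 |
| n per arm for 90% power, ten years | 7,500 | 28,277 | 18,648 |
| Men invited per death averted, ten years | 40 | 77 | 62 |
| Ten-year power, 7,500 per arm | 90% | 38.6% | 53.8% |
| Ten-year power, 23,604 per arm | not stated | 84.2% | 95.4% |

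A log-rank calculation by Schoenfeld's formula gives nearly the same five-year power: 38.5% and 53.7%.

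**4. Other readings of the inputs.**

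- One-sided 5% test (sidedness is not stated): power 51% or 66%; 72,955 or 48,036 per arm for 90%.
- 15% read as the risk of men without disease, so overall risk 0.88 × 15% + 0.12 × 28% = 16.56%: 97,182 or 64,015 per arm.
- Attendance ignored altogether: 0.224 + 0.50 = 0.724 points, power 60%, 171 lives.
- One-third factor dropped, attendance kept on medication: 0.504 + 0.375 = 0.879 points (power 77%) or 0.504 + 0.50 = 1.004 points (n = 25,841, power 87%).
- One-third factor dropped and attendance applied to the AAA part only: 0.672 + 0.375 = 1.047 points, n = 23,733, 247 lives.

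Of these, only the last comes close to the stated size and lives together, and it sets aside an input that the section lists.

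**The case against.** The strongest reply is that the inputs are loosely worded. If statin and antiplatelet treatment were each newly started in a separate third of diagnosed men, with additive 20% effects, the difference would be 0.711 points (attendance on both parts) to 0.948 points (attendance ignored), giving 59–83% two-sided power and 168–224 lives. That stands to this extent: 38–54% is the result of the literal reading, and neither it nor the 60% obtained by ignoring attendance is an upper bound. It does not restore 90% two-sided power or 250 lives. Moving to a one-sided test cannot help with the lives saved, which do not depend on the test.

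Four stronger readings are tempting, and the document does not support them.

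- *The trial is not viable.* Five years is not named as the decisive analysis, final results are due after 15 years, and ten-year power at 23,604 per arm is about 84–95%. The target group is the region's approximately 50,000 men of this age.
- *The cause is known.* Dropping the one-third factor comes close numerically, but the document does not say that this was done. How the error arose is conjecture.
- *The Background contradicts the AAA assumption.* It says that "only 352 Danish men above the age of 65 require AAA screening to avoid one AAA rupture-related death in the subsequent 5-year period", about 0.28 points against the 0.50 assumed. That figure concerns rupture-related death in earlier research; the planning input concerns AAA-related death in this trial. A different input for a differently worded endpoint is not an arithmetic contradiction, and it is not used here.
- *The word conservative has no basis.* It has one for omitted benefits: hypertension is expressly excluded, and only medication is counted although lifestyle advice is also given. It cannot be applied to the arithmetic, where the implied effect is 1.05/0.668 = 1.6 to 1.05/0.543 = 1.9 times what the inputs give.

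**Conclusion.** The stated results do not follow from the stated assumptions. They require a risk ratio of 0.93; the listed inputs give about 0.964–0.955. Read literally and two-sided, five-year power at 23,604 per arm is about 38–54%, not 90%, and expected lives saved are about 128–158, not 250. The ten-year arithmetic is consistent with 0.93, so its fault is the inherited ratio.

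The range rests on four readings: 12% combined prevalence without overlap, 15% as overall control mortality, attendance applied to the medication effect, and attendance either applied or not applied to the AAA effect. The finding is confined to a wrong statement of power, size and expected benefit on the primary outcome. It does not show that the trial needs more men or cannot answer its question in the long run.

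**What to change.** Take one of two routes in Power and expected benefit.

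1. Keep the assumptions and correct the results. Show the component calculation, say whether attendance applies to the AAA effect, and state whether the test is one- or two-sided. Restate power, size, lives saved and absolute reduction at five and ten years, as in the table. Give the number per death averted per man invited, since it comes from the intention-to-treat difference: about 62–77 at ten years.
2. Keep the risk ratio of 0.93, and correct and justify the assumptions that produce it. Deleting the one-third factor is not enough: with attendance applied to the medication effect, power is only 77–87%.

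In either case, limit the word conservative to the omitted benefits, such as hypertension. Naming ten years as the confirmatory time point for mortality is an optional design choice and would have to be squared with the planned 15-year final result.

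Under the first route the cost is rewording and less favourable published figures, with no additional men and no change to trial conduct. The second also requires support for the revised inputs.

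### The listed planning inputs give about 38-54% power at five years, not 90%; the AAA input also exceeds the protocol's own cited evidence, so the conservative label is unsupported

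*Protocol article*

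**What the plan says.** The section on power and expected benefit lists these assumptions:

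- Four per cent of the men have AAA and 8% have PAD.
- For baseline risk, the section states: "The five year mortality risk in case of AAA or PAD is 28% oppose to 15% in the control group".
- For prophylaxis, it assumes that medication can be started in one-third of those diagnosed, and that this "causes a relative all cause mortality risk reduction of 20" per cent.
- For the AAA gain, it assumes: "AAA-related death within five years is 1% but screening reduces this with 50" per cent.
- Three-quarters of invited men are expected to attend.

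From these it concludes that "the needed sample size is 2 × 23,604 (5% significance level and 90% power) and approx. 250 lives will be saved". A ten-year scenario follows: 36% control mortality, the same relative risk, 2 × 7,500 men, a 2.5% absolute reduction and 590 lives. The section closes with "These calculations must be considered to be conservative" and notes that benefit from newly found hypertension is left out.

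The Background gives the evidence. On AAA, "only 352 Danish men above the age of 65 require AAA screening to avoid one AAA rupture-related death" over five years. On prophylaxis, the measures "reduce the increased risks for cardiovascular disease by at least 20-25" per cent.

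**The concern.** The section prints its inputs, its result and a judgement on that result, so all three can be checked against each other. Two things do not fit. Multiplying the inputs gives roughly half the mortality difference that the sample size requires. And one input, the AAA gain, is larger than the figure the protocol cites for the same five-year horizon.

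All-cause mortality is the primary outcome and five years is a planned major follow-up. If that analysis shows no difference, readers will judge it against a stated 90% power that is described as conservative, and may conclude that screening does not work. The ten-year figures carry the same relative risk forward, so they inherit the problem.

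**Working it through.** **Method.** Two-proportion normal approximation, equal arms, two-sided 5%. The protocol does not state sidedness; two-sided reproduces its figure. Per arm, n = [1.960·√(2p̄(1−p̄)) + 1.282·√(p₁(1−p₁)+p₂(1−p₂))]² / (p₁−p₂)². Control risk p₁ = 15%. Lives saved = difference × 23,604 invited men.

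**Step 1: what the stated sample size implies.** A relative risk of 0.93 (15% v 13.95%, difference 1.05 points) gives n = 23,596 per arm and 0.0105 × 23,604 = 248 lives. The stated 23,604 and approximately 250 lives therefore agree with each other. At ten years, 36% × 0.07 = 2.52 points gives n = 7,501, and 2.5% × 23,604 = 590 lives, so these agree with the same relative risk.

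**Step 2: what the listed inputs give.**
- Prophylaxis: (4% + 8%) × 28% × 20% × 1/3 × 75% = 0.168 points.
- AAA: 1% × 50% = 0.5 points per man screened; × 75% = 0.375 points per man invited.

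| AAA part | Difference | Lives | n per arm for 90% | Power at 23,604 |
|---|---|---|---|---|
| 0.375 (attendance applied) | 0.543 | 128 | 89,512 | 38% |
| 0.5 (attendance not applied) | 0.668 | 158 | 58,938 | 54% |

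Of the combinations tried, the stated n was approached only by dropping the one-third and applying attendance to the AAA part alone: 12% × 5.6% + 0.375% = 1.047 points, n = 23,733. That contradicts the listed assumptions.

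**Step 3: the AAA input against the cited evidence.** 1/352 = 0.284 points. The Background does not settle whether 352 counts men screened or men invited.
- Men screened: 0.5 / 0.284 = 1.76 times the cited effect. Per man invited the cited effect becomes 0.75/352 = 0.213 points.
- Men invited: 0.375 / 0.284 = 1.32 times.

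Replacing only this input:
- 352 invited: 0.168 + 0.284 = 0.452 points, power 28%, n = 129,461 per arm.
- 352 screened: 0.168 + 0.213 = 0.381 points, power 21%, n = 182,578 per arm.

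**Step 4: how much of the shortfall is due to the AAA input.** Take the planned 1.05 points as given and swap only the AAA part (0.375 to 0.284 or 0.213). The difference becomes 0.959 or 0.888 points and power 84% or 78%. The larger loss comes from the multiplication in Step 2.

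**Step 5: the prophylaxis input, which depends on wording.** The section uses 20% of 28% = 5.6 points per treated man. If the Background's increased risk means only the excess, 20% × (28% − 15%) = 2.6 points, so prophylaxis contributes 12% × 2.6% × 1/3 × 75% = 0.078 points. With 0.213 for AAA the total is 0.291 points and power 14%; with 0.284 it is 0.362 points and 20%. If instead it means the cited 25-30% cardiovascular deaths, 20-25% of that is 5.0-7.5 points, which contains 5.6.

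**Step 6: ten years at 23,604 per arm, 36% control mortality, relative risk maintained.**

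| Basis | Relative risk | Difference | Power |
|---|---|---|---|
| Listed inputs, attendance on both parts | 0.964 | 1.30 | 84% |
| Listed inputs, attendance not on AAA part | 0.955 | 1.60 | 95% |
| 1 in 352 invited | 0.970 | 1.09 | 69% |
| 1 in 352 screened | 0.975 | 0.91 | 55% |

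**The case against.** The best defence is that several choices do lean conservative. Hypertension benefit is omitted. PAD is set at 8%, although the Abstract says around 10%. The 20% is the low end of the cited range, and only medication is counted although lifestyle advice is also given. These points are fair in direction but do not close the gap. With PAD at 10%, a 25% reduction and 1 in 352 per man invited, the difference is 0.75 × 14% × 1/3 × 28% × 25% + 0.284% = 0.529 points and power is 37%. Starting from the listed inputs, the hypertension benefit would have to supply 1.05 − 0.67 = 0.38 to 1.05 − 0.54 = 0.51 points, and the document gives no figure for it.

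A second defence is that the AAA comparison is not exact: the Background speaks of rupture-related death and the power section of AAA-related death, and the denominator of 352 is unclear. This stands as a caution. It is why both ratios are shown, but the input is the larger figure on either denominator.

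The defence also limits the point in three ways. A reader might infer that optimistic inputs are what brings 90% down; Step 4 shows that they are not the main cause. A reader might take the prophylaxis effect as plainly too large; that holds only on the excess-risk reading, and the protocol's own 25-30% cardiovascular mortality supports another. And a reader might conclude that the trial cannot detect its effect. Low five-year power is not zero power, and major follow-up continues to 10 years with the final result at 15.

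**Conclusion.** The five-year power statement is wrong as written. The listed inputs give 0.54-0.67 points, 128-158 lives and 38-54% power at 2 × 23,604, against the 1.05 points and approximately 250 lives on which the stated 90% rests. The AAA input is in addition 1.32 to 1.76 times the protocol's own cited effect; using 1 in 352 gives 0.38-0.45 points and 21-28% power. A figure of about 14% follows only if the prophylaxis effect is also limited to excess risk and 352 counts men screened. That is one reading and should not be quoted as the result. The conservative label is unsupported.

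These figures assume no overlap between AAA and PAD and that the 1% AAA death applies to all men. Overlap, or applying the 1% only to men with AAA, would lower the difference further. They also assume a two-sided test.

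**What to change.** Rewrite the power paragraph:

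1. Reconcile 2 × 23,604 and 250 lives with the listed inputs, or state the inputs that were actually used.
2. Use 1 in 352 for the AAA gain, saying whether it counts men invited or screened, or justify 1 in 200.
3. State the basis for a 20% reduction in all-cause mortality, given that the Background cites a reduction in increased cardiovascular risk.
4. Delete the statement that the calculations are conservative. The omission of hypertension benefit can stay as a remark on direction.
5. Give five-year power as a range, and recompute the ten-year figures (2 × 7,500, 2.5%, 590 lives) from the corrected relative risk.
6. State that a null five-year result does not exclude the planned benefit.

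The cost is one paragraph and a less favourable five-year power figure. Enrolment does not change.

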### Ethical considerations

This trial is approved by the regional scientific ethics committee and by the national data protection authorities. In accordance with the Clinical Trial Registration Statement from the International Committee of Medical Journal Editors, the trial is registered at clinical trials with the registration number NCT00662480.

## Discussion

The study population of men aged 65-74 years has been selected due to its relatively high cardiovascular risk, as most studies have reported increased risk with increasing age and lower prevalences of PAD and AAA in women. Nonetheless recent studies [21,22] indicates that the incidence of PAD in women is also considerable especially among elder women. Data on the prevalence and prognosis in woman are however too sparse at the moment to justify a parallel randomised trial but indeed it may be relevant to include women in a later stage, especially if the existing trial proves to be cost effective.

## Conclusions

The VIVA screening trial is a prospective randomized clinical trial examining the efficacy and cost effectiveness of a screening programme for early detection of AAA and PAD across 50,000 men aged 65-74 years. The primary outcome is all-cause mortality and secondary outcomes are AAA-related mortality, costs of hospital services related to cardiovascular conditions, quality of life, aneurismal progression and cost-effectiveness. Upon evaluation of outcome parameters after 3, 5, 10 and 15 years, this study will inform policy-makers about the attractiveness of introducing a national, permanent screening programme for cardiovascular disease
